# Effects of multimodal exercise program on postural balance in patients with chronic obstructive pulmonary disease: study protocol for a randomized controlled trial

**DOI:** 10.1186/s13063-023-07558-9

**Published:** 2023-08-15

**Keywords:** Breathing exercises, Electric stimulation, Postural balance, Rehabilitation, Randomized controlled trial

## Abstract

**Background:**

Evidence has shown that patients with chronic obstructive pulmonary disease present significant deficits in the control of postural balance when compared to healthy subjects. In view of this, it is pertinent to investigate the effects of different therapeutic strategies used alone or in association with pulmonary rehabilitation with the potential to improve postural balance and other outcomes with clinical significance in patients with chronic obstructive pulmonary disease. This study will investigate the effects of an 8-week (short-term) multimodal exercise program [inspiratory muscle training (IMT) plus neuromuscular electrical stimulation (NMES)] on postural balance in patients with chronic obstructive pulmonary disease enrolled in a pulmonary rehabilitation program compared to individualized addition of IMT or NMES to pulmonary rehabilitation or standard pulmonary rehabilitation.

**Methods:**

This is a randomized, single-blind, 4-parallel-group trial. Forty patients with chronic obstructive pulmonary disease will be included prospectively to this study during a pulmonary rehabilitation program. Patients will be randomly assigned to one of four groups: multimodal exercise program (IMT + NMES + pulmonary rehabilitation group) or (IMT + pulmonary rehabilitation group) or (NMES + pulmonary rehabilitation group) or standard pulmonary rehabilitation group. Patients will receive two sessions per week for 8 weeks. The primary outcome will be static postural balance and secondary outcomes will include as follows: static and dynamic postural balance, fear of falling, muscle strength and endurance (peripheral and respiratory), functional capacity, health-related quality of life, muscle architecture (quadriceps femoris and diaphragm), and laboratory biomarkers.

**Discussion:**

This randomized clinical trial will investigate the effects of adding of short-term multimodal exercise program, in addition to pulmonary rehabilitation program, in postural balance in patients with chronic obstructive pulmonary disease enrolled in a pulmonary rehabilitation. Furthermore, this randomized control trial will enable important directions regarding the effectiveness of short-term intervention as part of the need to expand the focus of pulmonary rehabilitation to include balance management in chronic obstructive pulmonary disease patients which will be generated.

**Trial registration:**

ClinicalTrials.gov NCT04387318. Registered on May 13, 2020.

## Background and rationale {6a}

### Background

Oxidative stress is involved in the pathogenesis and progression of chronic obstructive pulmonary disease (COPD) causing cell damage [1]. In this scenario, clinical studies demonstrate in DNA a significant increased damage and inefficiency in repair mechanisms which may lead to genomic instability and cellular senescence in patients with COPD [2]. The primary pathophysiology of COPD is related to damage to the respiratory system [3]. However, the respiratory and limb muscle dysfunction appears to be a major systemic manifestation in COPD [4], contributing to reduction in functional capacity and health-related quality of life (HRQoL) [5].

A recent meta-analysis showed that compared with healthy controls, patients with COPD have a clinically meaningful balance reduction [6]. Balance impairment is one of the main risk factors for falls, and patients with COPD are four times more likely to fall than their healthy peers, leading to increased morbidity and mortality [6, 7].

Because COPD is a complex and systemic disease, its treatment requires an integrated therapeutic approach, including the referral for pulmonary rehabilitation (PR) [3]. PR has been demonstrated to reduce dyspnea and improve exercise capacity and HRQoL; its core components include aerobic and strength training [8, 9]. However, despite accumulating evidence on balance impairment in patients with COPD, routine assessment of this outcome is still not an included in PR [8, 9]. The American Thoracic Society (ATS)/European Respiratory Society (ERS) Statement on PR briefly presents a broadened scope of outcomes assessments in PR, including balance. Nevertheless, the focus of PR should be expanded to include the assessment, training, and elucidation of the potential mechanisms underlying balance deficits in COPD [6].

Respiratory and limb muscle dysfunctions are particularly relevant in the COPD because they contribute to balance impairments [4, 6, 10]. In this sense, it is worth noting that the diaphragm plays an important role in postural balance and the impairment function of this muscle observed in COPD contributes to the deterioration in balance [11]. Therefore, it is reasonable to infer that a multimodal exercise program [inspiratory muscle training (IMT) plus neuromuscular electrical stimulation (NMES)] could potentially improve postural balance. These therapeutic strategies have been used to complement PR [12, 13]. However, no study has assessed the efficacy of short-term multimodal exercise programs in addition to PR in patients with COPD.

## Objectives {7}

Therefore, this study aims to investigate the effects of short-term multimodal exercise program (IMT plus NMES) compared to individualized addition of IMT or NMES to PR or standard PR on postural balance, fear of falling, muscle strength and endurance (peripheral and respiratory), functional capacity, HRQoL, muscle architecture (quadriceps and diaphragm), inflammatory profile, endothelial function, oxidative stress and DNA damage in patients with COPD. We hypothesize that the addition of a multimodal exercise program could potentiate the aforementioned outcomes.

## Trial design {8}

This is a protocol for a clinical, randomized, controlled, single-blind (outcomes assessor), four-arm parallel-group, and framework superiority study. Patients will be randomized (1:1:1:1). This study was approved by the ethics committee (process no. 3.208.982). The protocol will be conducted according to the Consolidated Standards of Reporting Trials (CONSORT) statement. The trial was registered at ClinicalTrials.gov (“X”).

## Methods: participants, interventions, and outcomes

### Study setting {9}

This will be a single-center study carried out at the PR program at the University Hospital of Santa Maria, Rio Grande do Sul, Brazil.

### Eligibility criteria {10}

The eligibility criteria include patients aged 55 years or more (adult, older adult) of both sexes.

#### Inclusion criteria

Clinical diagnosis of COPD, stages II, III, or IV [3];Clinically stable, i.e., absence of infections or exacerbations in the last 3 months;Medical clearance to participate in PR;Availability of attending to the PR.

#### Exclusion criteria

Unstable primary pathologies (cardiovascular, renal, metabolic, or psychiatric);Nutritional aspects (nutritional supplementation on the 4 weeks preceding the study or obesity (BMI>30 kg/m^2^));Severe hearing, visual or vestibular disorder impairment recorded on patient chart or self-referred;Evidence of a neurological or musculoskeletal condition that severely limits mobility and postural control;Contraindications to NMES;Participation in PR programs in the 3 months previous to the study or physically active;Active smoker and/or active alcohol;Cognitive impairment.

All eligible patients will undergo the same assessments at the beginning and after 8 weeks of the study (Fig. 1).

**Fig. 1 Fig1:**
[figure not shown]
CONSORT flowchart of the planned protocol pathway. HRQoL: Health-related quality of life; IMT: Inspiratory muscle training; NMES: Neuromuscular electrical stimulation; PR: Pulmonary rehabilitation

### Who will take informed consent? {26a}

The [name] researcher will be in charge of contacting potential participants whose names are on the waiting list to start PR and invite them to participate in the study. If we have a positive reply, an appointment will be scheduled, and the [name] will explain the objectives of the study, risks, benefits, and ethical implications. If participants agree to participate in the study, they will be asked to sign two copies of an informed consent form: one for the participants and the other for the researcher.

### Additional consent provisions for collection and use of participant data and biological specimens {26b}

We will request consent from participants for the collection of blood samples to assess biomarkers, endothelial function, oxidative stress, muscular damage, and DNA damage.

## Interventions

### Explanation for the choice of comparators {6b}

After baseline evaluations, all patients will receive the proposed therapeutic modality according to the group to which they will be randomly assigned (Fig. 2). All interventions will occur under the direct supervision of a physical therapist with more than 5 years of clinical experience, aiming to improve adherence to intervention protocols (blinded to outcome assessment), for 8 weeks, twice per week, for a total of 16 sessions. Vital signs will be continuously monitored, and possible adverse events will be recorded.

**Fig. 2 Fig2:**
[figure not shown]
Sequence and type of therapeutic modality proposed in each study group. IMT: Inspiratory muscle training; NMES: Neuromuscular electrical stimulation; PR: Pulmonary rehabilitation

### Intervention description {11a}

#### Inspiratory muscle training

Patients randomized to the (IMT + NMES + PR) and (IMT + PR) groups will undergo IMT using the POWERbreathe Medic Plus (POWERbreathe Medic Plus®, SP, BR). The initial training load will be at 30% of the MIP (obtained by manovacuometry) during the first 2 weeks to allow for an adjustment period. Load increases will occur as follows: 35% of MIP in week 3, 40% of MIP in week 4, 45% of MIP in week 5, 50% of MIP at week 6, 55% of MIP in week 7, and 60% of MIP in weeks 8. The IMT will consist of five sets of 10 repetitions each, with a 1-min interval between each set, twice a week for 8 weeks. During training, patients will be instructed to maintain diaphragmatic breathing. In order to get feedback regarding perceived inspiratory effort, the modified Borg CR10 scale (4–6 out of 10) will be considered.

#### Neuromuscular electrical stimulation (NMES)

The (IMT + NMES + PR) and (NMES + PR) groups will receive the NMES for 16 sessions (2 days per week for 8 weeks). NMES will be applied bilaterally using an electrical stimulator (Neurodyn II, model N53, IBRAMED, SP, BR) with one proximal electrode (7.5 × 13 cm) at the motor point of the quadriceps muscle and another distal electrode above the upper pole of the patella [14]. The patient will be placed in the dorsal decubitus position, lower limbs on a foam wedge, and knees flexed at 60° [14]. The NMES protocol will consist of the application of symmetrical biphasic rectangular pulses, 50 Hz frequency, 400 ms pulse width, stimulation (ON) time of 5 s, and relaxation (OFF) time of 15 s (first month), and 10 s ON and 30 s OFF (second month). The maximum intensity tolerated progressively will be used, which should culminate in visible and comfortable muscle contraction [14, 15].

#### Pulmonary rehabilitation program

All patients will undergo the PR program for approximately 60 min per session. Firstly, aerobic training will be performed on a cycle ergometer (Kikos kr5.6 bivolt, SP, BR) for 30 min; the initial training intensity target will be 60% of the maximum work rate [16]. The increase in exercise intensity will be based on the rating of perceived exertion (4–6 on the modified Borg scale [8, 9]). Furthermore, the heart rate target will be kept between 50 and 80% of resting HR [8]. Three sets of eight repetitions will be performed at intensities initially defined as 50% of the one-repetition maximum (1RM) with weekly increases until it reaches 80% of the 1RM at the end of 8 weeks [8, 9].

### Criteria for discontinuing or modifying allocated interventions {11b}

Patient withdrawal from the study will only occur if consent is obtained. The presence of clinical instability is the criterion for discontinuing the interventions. However, patient follow-up will proceed normally; that is, the patient will not be excluded from the analyses (reassessments).

### Strategies to improve adherence to interventions {11c}

Patients will individually receive a report at the end of the study, with the performance obtained in the evaluations at pre- and post-intervention. Moreover, every session will be overseen by a researcher with experience in exercise rehabilitation to ensure that the patients perform the exercises properly.

### Relevant concomitant care permitted or prohibited during the trial {11d}

Participants are allowed to maintain their pharmacological treatment throughout the study. Participants will be excluded in case of any modification of the dose or type of drug during the trial. Furthermore, patients will be instructed not to perform any other form of exercise during the intervention.

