### Plans to promote participant retention and complete follow-up {18b}

The participants who enroll in the study in each session will be asked to provide feedback regarding their health status. Participants will receive a schedule with the dates and times for the assessment and training, in addition to a text message to remind them of the training schedule. An intention-to-treat analysis will be applied to include all randomized participants.

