### Methods in analysis to handle protocol non-adherence and any statistical methods to handle missing data {20c}

Intention-to-treat analysis will be applied to include all randomized participants. Thus, the participants will be analyzed in the groups to which they will be allocated, even if they do not complete the intervention protocol (reassessments are intended for all patients). If this is not possible, the missing data will be handled using a multiple imputation method.

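### The rule in {11d} that excludes participants for any drug change conflicts with the protocol's intention-to-treat rule and could remove randomised patients from the primary comparison

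*Protocol article*

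**What the plan says.** The section on concomitant care {11d} lets participants continue their drug treatment, then adds: "Participants will be excluded in case of any modification of the dose or type of drug during the trial". It covers any drug, any dose change and the whole trial period. It names no analysis set.

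The other sections point the opposite way:

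- {11b}, on withdrawal: "Patient withdrawal from the study will only occur if consent is obtained".
- {11b}, on stopping the intervention: "The presence of clinical instability is the criterion for discontinuing the interventions". Follow-up of such a patient continues, and "the patient will not be excluded from the analyses (reassessments".
- {18b}: "An intention-to-treat analysis will be applied to include all randomized participants".
- {20c}: "Intention-to-treat analysis will be applied to include all randomized participants". Participants are analysed as allocated even if they do not complete the intervention, "reassessments are intended for all patients", and multiple imputation is the fallback.

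**The concern.** Read as written, {11d} takes randomised people out of the trial because of something that happens after randomisation. Patients with COPD may have a drug changed because their clinical state has changed. Only the outcome assessors are blinded, so knowledge of the allocated arm could also play a part. If the chance of exclusion, or the kind of patient excluded, differs between arms, the groups left at 8 weeks are no longer those that randomisation formed.

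The conflict also falls on a single patient. Someone who becomes clinically unstable and has a drug changed is kept under {11b} and excluded under {11d}. What is at stake is who enters the primary analysis of postural sway, in arms planned at only 10.

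**Working it through.** **1. The rules side by side**

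| Situation | {11b} | {11d} | {18b} and {20c} |
|---|---|---|---|
| Intervention stopped for instability, no drug change | followed up and analysed | silent | analysed |
| Drug or dose changed, patient stable | no ground for withdrawal | excluded | analysed |
| Unstable and drug changed | followed up and analysed | excluded | analysed |

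The second and third rows give incompatible instructions. No section limits the {11d} exclusion to a per-protocol set or says which rule prevails.

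**2. The plan's own sample size**

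Section {14} gives 10 per group (40 in total) at p < 0.05, 80% power and 20% loss. It prints ±12.1 mm and ±7.2 mm for COPml (mediolateral sway amplitude), without saying whether these are means or SDs. A sample size needs both a difference and an SD, so the figure can be neither reproduced nor refuted. If 10 already includes the loss, there are 10 × 0.8 = 8 evaluable per arm. With a two-sided 5% t test (sidedness assumed), 80% power at 8 per arm implies a standardised difference of 1.51.

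- If the values are means, the difference is 12.1 − 7.2 = 4.9 mm and the implied SD is 4.9 / 1.51, about 3.3 mm.
- If the values are SDs, the pooled SD is √((12.1² + 7.2²) / 2) = 9.96 mm, about 10 mm.

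**3. Possible bias**

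Let p₁ and p₀ be the proportions excluded in two arms, and let δ be the amount by which excluded patients sway more than retained patients in the same arm. Dropping a proportion p lowers an arm's mean by p × δ, so the size of the bias in the arm difference is (p₁ − p₀) × δ. Take δ = 1 SD. Both δ and the proportions are assumptions, as the article gives neither.

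| Excluded, arm 1 v arm 2 | Bias in SDs | SD 3.3 mm | SD 9.96 mm |
|---|---|---|---|
| 20% v 0% (2 of 10 v none) | 0.20 | 0.66 mm | 1.99 mm |
| 10% v 0% (1 of 10 v none) | 0.10 | 0.33 mm | 1.00 mm |
| equal in both, same δ | 0 | 0 | 0 |

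On these assumptions the 20% v 0% case is 0.20 / 1.51, about 13% of the standardised difference implied in step 2.

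**4. Possible loss of power**

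At a standardised difference of 1.51, the power of a pairwise comparison is 80% with 8 evaluable per arm, 73.5% with 7, 65% with 6 and 55% with 5. This applies only to exclusions beyond the planned 20% loss.

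**The case against.** The best defence is that {11d} is a concomitant-care item. It says excluded, but not excluded from the analyses, whereas {11b} names the analyses when it means them. If {11d} only ends treatment, {20c} still analyses the participant as allocated. An analyst working from {18b} and {20c} alone has one clear instruction, with imputation as a fallback.

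That reading is possible, but the text does not state it. It also creates a second conflict, because {11b} gives clinical instability as the one criterion for stopping the intervention. The ambiguity is itself a reason to reconcile the sections.

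Several stronger inferences are tempting, and here the defence is right that the document does not support them:

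- **Drug changes are outcome-related.** The article does not say why drugs would change. {11d} covers drugs unrelated to COPD, and the primary outcome is force-platform sway. The link is plausible, not established.
- **Instability followed by a drug change is the usual case.** No frequency is given.
- **Exclusions come on top of the planned 20% loss.** {14} does not define loss, so they may already fall within it.
- **The bias is 2 mm.** That needs an SD near 10 mm, which {14} does not fix. Two exclusions against none in arms of 10 is also an extreme split. Multiple imputation could reduce the bias if excluded patients were treated as missing.
- **Patients have already been removed.** No such exclusion is reported.

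**Conclusion.** The contradiction stands on the wording alone and needs none of the assumed figures. {11d}, followed as written, could remove randomised participants whom {11b}, {18b} and {20c} keep. It affects the primary analysis set, so it should be settled before the results are relied on.

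Its numerical effect is unknown. An illustrative bias of about 0.7 to 2 mm rests on 20% against 0% excluded, a 1 SD shift, and SDs of 3.3 to 10 mm taken from the two readings of {14}. It is smaller with less imbalance, and zero if no one was removed. A reader might conclude that the trial's result is already biased, but the article shows only that its rules would permit this.

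**What to change.** Reconcile {11b}, {11d}, {18b} and {20c} by stating that {11d} does not define the analysis set. A change of drug or dose is recorded as a protocol deviation. The participant stays in the 8-week reassessment and the intention-to-treat analysis, with multiple imputation under {20c} if no reassessment exists. Whether a drug change affects continued training is a clinical matter for the investigators; the text should state it consistently in {11b} and {11d}.

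The trial status is given as completed, so the final report should also:

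- give, by arm, the number of participants removed under {11d}, including zero if none;
- restore any such participants to the primary analysis;
- present any analysis without them as a sensitivity analysis only.

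The text change costs a sentence or two, and the count comes from trial records. If anyone was removed before reassessment, that 8-week measurement can no longer be recovered and must be imputed. If no one was removed, the primary analysis is unchanged.

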### Provisions for post-trial care {30}

There was no anticipated harm or compensation for participating in the trial. At the end of the study, participants interested in continuing PR will be referred to the university hospital for outpatient care.

### Outcomes {12}

The results will be evaluated at two time points: (1) baseline (before starting the intervention program) and (2) after 8 weeks of intervention. Trained assessors will conduct all assessments and reassessments. The evaluators will be physical therapists with at least 1 year of training experience in the evaluation instruments used in this study.

#### Primary outcome

##### Static postural balance

The primary outcome will be measured using the AMTI portable force platform model OR6-6-2000 (Advanced Mechanical Technologies, Inc.) with an acquisition frequency of 100 Hz [17]. Standardized verbal instructions will be used to guide proper patient positioning. Three attempts lasting 30 seconds each, with 1 minute rest in between, will be performed (eyes open and then closed) and the average will be considered for analysis [18].

Body sway will be evaluated from the center of pressure (COP) and the variables will comprise COP anteroposterior displacement amplitude (COPap), COP mid-lateral displacement amplitude (COPml), COP displacement velocity (COPvel) and 95% ellipse area (AE). Then, the raw data obtained will be filtered using a fourth-order zero-lag Butterworth with 10 Hz cut-off frequency, and processed using custom Matlab routines (R2020a, The Mathworks, Inc., Massachusetts, USA).

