### Sample size {14}

Based on the data from a previous study, performed by Mekki et al. [13] (*n*=45 participants, conducted in Tunisia), it will be necessary in a minimum sample size of 10 individuals per group and a total of 40 patients, considering the variable of mean lateral displacement of the pressure center mid-lateral displacement amplitude (COPml) in the follow-up of the intervention group, which performed NMES associated with PR program (±12.1 mm) and the control group that only performed standard PR (±7.2 mm). We also considered *p* value <0.05, power of 80% and loss of 20%.

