## Statistical methods

### Statistical methods for primary and secondary outcomes {20a}

The data will be analyzed using GraphPad Prism 5 (GraphPad Software Inc., San Diego, CA, USA). The normality of variables will be assessed by the Shapiro-Wilk test. The continuous variables with normal distribution and those with non-normal distribution will be presented as mean ± standard deviation (SD), 95% confidence interval (95% CI), and median (interquartile range), respectively, while categorical variables will be presented as absolute frequencies and percentages. Student’s *t* test for paired samples (parametric data) or Wilcoxon test (non-parametric data) will be used to compare the results before and after the intragroup intervention according to data distribution, and the effect size will be calculated using Cohen’s d. Comparison between groups will be performed using two-way analysis of variance (ANOVA) with repeated measures, followed by Bonferroni’s post hoc. Effect size was calculated using Cohen’s d. The significance level will be set at 5% (*p* <0.05).

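### The primary outcome is four centre-of-pressure variables in two visual conditions with none named as primary, so the 5% level does not cover a primary claim taken across them

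*Protocol article*

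**What the plan says.** The abstract (Methods) names a domain, not a variable: "The primary outcome will be static postural balance". The Outcomes section {12}, under Primary outcome, fills the domain with force-platform measures: "the variables will comprise COP anteroposterior displacement amplitude (COPap), COP mid-lateral displacement amplitude (COPml), COP displacement velocity (COPvel) and 95% ellipse area (AE)". All four are listed on a par. The same section says that three 30-second attempts "will be performed (eyes open and then closed) and the average will be considered for analysis". The domain label does not identify the endpoint by itself, because static postural balance appears again among the secondary outcomes, measured by posturography.

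Sample size {14} uses one of the four variables, "pressure center mid-lateral displacement amplitude (COPml) in the follow-up of the intervention group", against the standard-rehabilitation group. It does not call COPml the primary variable and does not say whether eyes were open or closed.

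Statistical methods {20a} sets a single 5% significance level and compares groups by "two-way analysis of variance (ANOVA) with repeated measures, followed by Bonferroni’s post hoc". The ANCOVA in {20b} is described as supportive. Trial status gives the trial as completed, and {16c} says that analyses will be blinded.

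**The concern.** A 5% level protects a primary claim only if one test carries the claim, or if the plan says how several tests combine. Here several measures share primary status and nothing says which decides. The Bonferroni step does not fill the gap: it follows each ANOVA and handles comparisons within that variable, whereas the open question lies across variables and visual conditions.

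A report could therefore present a significant result on any one of these measures as the primary finding and still be consistent with the protocol. With 10 patients per group, chance findings on single sway measures are a practical risk. The variable on which the trial was sized might not be the one on which success is claimed.

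**Working it through.** **The plan's own figure.** Sample size {14} gives 10 per group. The dropout step fits 8 evaluable patients per group: 8 / (1 − 0.20) = 10. The 8 itself cannot be reproduced, because ±12.1 mm and ±7.2 mm are given without saying whether they are means or standard deviations. That is a separate matter. Here the section matters only because it makes COPml the sized variable and fixes 10 per group.

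**Inputs.** Four variables and two visual conditions ({12}); 5% level and Bonferroni after each ANOVA ({20a}); four groups of 10 ({8}, {14}). The correlation between measures is not given, so 0.5 to 0.9, equal for every pair, is assumed.

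**Step 1, number of primary measures.** If the average is over the three attempts, which is the more natural reading: 4 × 2 = 8. If it pools the two visual conditions: 4.

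**Step 2, ceiling under independence, each measure tested at 5%.**
- Four measures: 1 − 0.95^4 = 0.185
- Eight measures: 1 − 0.95^8 = 0.337

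**Step 3, correlated measures.** With two time points, the group-by-time F test equals a one-way F test on change scores, with 3 and 36 degrees of freedom for four groups of 10. The protocol does not say which ANOVA term decides; the interaction is assumed. Simulating this test with no true effect (200,000 trials per cell) gives the chance that at least one measure reaches p < 0.05:

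| Correlation | Four measures | Eight measures |
|---|---|---|
| 0.5 | 16.1% | 26.5% |
| 0.7 | 13.6% | 20.6% |
| 0.8 | 12.2% | 17.2% |
| 0.9 | 9.8% | 12.8% |

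Two-sided normal tests in place of the F test give slightly lower values: 15.5% and 25.1% at 0.5, 9.4% and 12.0% at 0.9.

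**Step 4, what the Bonferroni step does cover.** Four groups give 4 × 3 / 2 = 6 pairs. If all six are compared, one pair is tested at 0.05 / 6 = 0.0083 within each variable. For that one pair across independent variables:
- Eight variables: 1 − (1 − 0.0083)^8 = 6.5%
- Four variables: 3.3%

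If only three pairs are compared, the level is 0.05 / 3 = 0.0167, and eight independent variables give 12.6%. The protocol does not state the number of pairs.

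**Step 5, price of adjusting across all measures instead.** Bonferroni levels would be 0.05 / 4 = 0.0125 or 0.05 / 8 = 0.00625. For an effect that gives 80% power at 0.05 in a two-sample t test with 8 or 10 evaluable per group, power falls to about 57–58% or 45–47%. Naming one variable in one condition keeps the 5% level and the sample size.

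**The case against.** The strongest reply is that COPml is already the implied primary, since the variable on which a trial is sized is ordinarily the lead variable. This has weight: COPml does have some standing, and it would be wrong to say it has none. But {14} does not designate it and {12} lists it second of four without distinction. Even if it is accepted, its visual condition stays open. Two tests remain, with an independence ceiling of 1 − 0.95^2 = 9.75%.

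A second reply is that adjustment across variables is commonly left to an analysis plan, and this is a condensed article. That stands for the adjustment. It does not stand for the designation of the primary variable, which {12} settles by naming four.

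A third reply concerns size. A reader might infer a 34% false-positive rate, or that each comparison between two groups is tested at 5% on eight variables. The documents support neither. The 34% requires independence, which is implausible for amplitude, velocity and ellipse area taken from the same platform recordings. A single pairwise contrast is Bonferroni-adjusted, so the figures for it are those in step 4. A reader might also infer a rule that any one significant measure counts as success. No such rule is written. An all-must-succeed rule would not inflate the error rate, but none is written either.

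**Conclusion.** The point holds in a limited form. The protocol designates no single primary variable or visual condition, uses COPml for sizing without calling it primary, and controls error only within each variable's ANOVA.

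At the level of that ANOVA test, the chance of at least one false-positive primary result is about two to five times the nominal 5% over the ranges in step 3. The independence values are ceilings. The result rests on assumed equal correlations, on the group-by-time test deciding, and on a claim being allowed from any one measure, which the text leaves open rather than states. The direction is the same under either reading of the averaging. It matters because it concerns the trial's main claim and is cheap to settle.

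**What to change.** In {12} and {20a}, name COPml in one stated visual condition as the single primary variable. State that the average is over the three attempts within a condition, if that is what is meant. Make the other COP variables and the other condition secondary, either Holm-adjusted or reported as estimates with 95% confidence intervals and no claim of success.

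Timing decides how far this can be relied on. The trial is listed as completed, and the documents do not show whether group codes have been opened, although {16c} plans blinded analysis. If the codes are still closed, the choice should be recorded and dated before they are opened. If they are open, the choice should be disclosed as made after data collection, and all the COP results reported together with a Holm adjustment.

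The cost is a short text change with no extra data and no change in sample size. The other COP variables lose primary status, and under {25} the change must go to the ethics committee and be entered in the registry.
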